### Study duration

The study period is defined as being 12 weeks on a particular course of treatment. Where patients continue treatment beyond 12 weeks, those being treated at home can continue to do so. However, if they prefer to be treated in hospital they can transfer. Those patients randomised to hospital treatment cannot cross over to treatment in the community, since community-based treatment is not standard practice locally. Patients stopping treatment earlier than 12 weeks are not replaced in the study, but the reason for stopping is noted. They are included for the collection of study outcomes at 12 weeks, since analysis is on an intention-to-treat basis.

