### Study interventions

The Investigator has primary responsibility for the welfare of the patient for the duration of the study, whether receiving treatment in hospital, at home or in the GP surgery. Patient treatment is governed by a single set of standard operating procedures in use at CUH, WSH (and the GP surgeries involved in this study.

The Investigator is responsible for prescribing all treatment for trial patients, but can delegate this task to a member of his or her junior staff, as is standard clinical practice.

The treatment study period for this trial is 12 weeks, since most treatments are expected to be prescribed for at least this period of time. All planned treatment for a study patient will be delivered in the location to which the patient is randomised. Treatment of patients within the community may be aborted and transferred to hospital in the event of significant problematic drug-related toxicities, occurrence of a serious adverse event (SAE), on request by the patient, or following discussion between the community chemotherapy nurse and the Investigator who may feel it is in the patient's best interest to do so. The Investigator will review the patient in clinic prior to study entry and on completion of the study (whether at 12 weeks, or sooner in the case of early withdrawal). For patients continuing treatment beyond 12 weeks, the Investigator will review the patient on completion of the planned treatment or at 24 weeks, whichever is sooner.

All anticancer treatment and other prescribed drugs are dispensed by the oncology pharmacists in the respective hospitals, according to local policies. On the designated day, prescribed drugs for patients receiving treatment in the community are dispensed and placed with a copy of the patient prescription sheet in a designated box, ready for collection by the community chemotherapy nurse from the oncology pharmacy at a previously arranged time. The prescription sheet copy is returned to the oncology pharmacy within 48 hours of treatment.

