### Recording and collection of data

Upon randomisation of an individual patient, a pack containing specifically designed data collection forms, questionnaires and diaries is provided to the Investigator. The forms allow collection of essential information required for the study at each predefined trial data collection point. The study has four mandatory and 1 optional data collection point. Mandatory data collection points are baseline (at the start of study treatment), then approximately 4 weeks, 8 weeks and 12 weeks after commencing treatment. For patients continuing treatment beyond 12 weeks, there is an optional data collection point at 24 weeks or on stopping treatment, whichever occurs sooner. The baseline, 12 week and 24 week data collection visits take place at hospital. On these occasions, study forms will be completed by the Investigator or a member of his/her team, which may include a specialist or research nurse/practitioner. Patient questionnaires and diaries are given to the patient and/or collected from the patient as appropriate at these visits.

In order to allow for different treatment schedules, the second and third data collection points may be flexible to within 1 week either side of the planned 4 and 8 week time points. For patients having treatment in hospital, on these occasions, forms are completed by the Investigator or a member of his/her team, which may include a specialist or research nurse/practitioner. Patient questionnaires are given to and collected from the patient as appropriate at these visits. For patients having treatment in the community, these study forms are completed by the community chemotherapy nurse. Patient questionnaires are given to and collected from the patient as appropriate at these visits.

Following each planned data collection point, study forms and questionnaires are returned to the Outreach Trial Coordinator, who is responsible for creating and completing the unique patient Case Report Forms (CRF).

Patients randomised to receive treatment in either community setting may be transferred at any time to continue treatment in hospital, and the date and reason for transfer will be documented. Transfer of care to the hospital constitutes a serious adverse event (SAE) and withdrawal from the trial. Patients randomised to receive treatment in hospital may not be transferred to either location in the community, since this is not standard clinical practice locally.

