###### vii) Impact of treatment on local GP resources

Once a patient has completed the trial, a letter is sent to the patient's own GP requesting review of the patient notes held at the local GP surgery to document: the number of occasions the patient contacted his or her GP surgery during the trial period; what type of surgery staff were involved on each occasion (e.g. GP, nurse, other); the nature of those contacts, by classifying them as being related to a) cancer treatment, b) other need for treatment of any kind, c) support services, d) advice, or e) other. In addition, a summary print-out of all prescriptions is requested. The GPs receive a small remuneration for providing this information.

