### Sample size

The EORTC QLQC30 questionnaire is a well validated instrument; this has been in widespread use since 1993 and is frequently used to assess quality of life of cancer patients in clinical trials. It comprises 30 questions representing various dimensions of quality of life. Of the 5 functional dimensions, emotional function might be considered to best reflect the levels of anxiety and satisfaction felt by patients taking part in this study. Using data on quality of life dimension mean scores determined by researchers interested in interpreting the results of the QLQC30 questionnaire, the standard deviation of the mean quality of life emotional function score for a large group of heterogeneous cancer patients is determined to be 24 [18,19].

With 130 patients randomised per arm, there is 80% power to detect a 10-point difference in mean QLQC30 score between any two study populations, at the 5% level of significance assuming a standard deviation 24. This allows for up to 30% of patients not providing information on the primary outcome, for reasons including withdrawal and non-completion of questionnaire. There is also 90% power to detect a 10-point difference between the home and GP surgery arms combined versus hospital using data from all three arms.

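### Counting every community-to-hospital transfer as withdrawal from the trial conflicts with the intention-to-treat commitment and risks one-sided, outcome-related loss of 12-week data

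*Protocol article*

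**What the plan says.** All places are in the protocol article.

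- *Recording and collection of data* sets the rule: "Transfer of care to the hospital constitutes a serious adverse event (SAE) and withdrawal from the trial".
- The same section makes it one-sided. On the community arms: "Patients randomised to receive treatment in either community setting may be transferred at any time to continue treatment in hospital". On the control arm: "Patients randomised to receive treatment in hospital may not be transferred to either location in the community".
- *Study interventions* gives the grounds for transfer: "significant problematic drug-related toxicities, occurrence of a serious adverse event (SAE), on request by the patient", or the Investigator's view, after discussion with the community nurse, of the patient's best interest.
- *Study duration* says of patients who stop treatment before 12 weeks: "They are included for the collection of study outcomes at 12 weeks, since analysis is on an intention-to-treat basis".
- *Study interventions* times the Investigator's closing review "on completion of the study (whether at 12 weeks, or sooner in the case of early withdrawal").
- *Sample size* names withdrawal as a source of missing primary outcome: "This allows for up to 30% of patients not providing information on the primary outcome, for reasons including withdrawal and non-completion of questionnaire".
- *Serious adverse events* lists the switch to hospital as an SAE but does not call it withdrawal.
- *Statistical Analysis* fixes 12 weeks as the primary time-point and home plus GP surgery versus hospital as the primary contrast. It plans a comparison of missing data by arm, a model for dropout, and sensitivity analyses.

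**The concern.** Read together, these sections treat two kinds of patient inconsistently. A patient who gives up treatment altogether is followed to 12 weeks. A patient who carries on with treatment in hospital is withdrawn. That cannot be squared with analysis by randomised arm, because a change of venue after randomisation is exactly what intention-to-treat is meant to absorb.

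The label has consequences, since the article elsewhere ties withdrawal to an early end of study and to absence of the primary outcome. A site that follows the rule could reasonably stop issuing questionnaires after a transfer. Data at risk are the 12-week QLQ-C30 and other questionnaires, the 12-week CSRI that feeds the economic analysis, and later adverse events, which are recorded only up to the final trial visit.

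The loss would fall only on the home and GP surgery arms, which form one whole side of the primary contrast. It would also be selective. Toxicity, an SAE, the patient's own request and the Investigator's concern all plausibly relate to emotional function, satisfaction and resource use.

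**Working it through.** **1. Reproduce the plan's figures.** Inputs from *Sample size*: difference 10, SD 24, 5% level (taken as two-sided), 30% missing, 130 per arm. Allocation is 1:1:1.

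- Evaluable per arm: 2 × (1.96 + 0.8416)² × 24² / 10² = 90.4, so 91.
- Randomised per arm: 91 / (1 − 0.30) = 130.
- Pairwise power with 91 versus 91: 80.3%.
- Primary contrast, 91 hospital versus 182 community: SE = 24 × √(1/91 + 1/182) = 3.08, and power = Φ(10/3.08 − 1.96) = 90.1%.

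The stated 130, 80% and 90% all reproduce. The sample size is not in question.

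**2. Set up the loss.** Let t be the share of community patients who transfer and are then lost, and D the number of points by which their 12-week mean lies below that of patients who stay. Neither is in the document; both are assumptions. If those who stay have mean M, the full community mean is (1 − t)M + t(M − D) = M − tD. Dropping the transferred patients therefore raises the observed community mean by t × D.

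**3. Bias and type I error with no true difference.** SE = 24 × √(1/91 + 1/(182(1 − t))). Type I error = 1 − Φ(1.96 − tD/SE) + Φ(−1.96 − tD/SE).

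| t | D | SE | Bias (points) | Type I error |
|---|---|---|---|---|
| 10% | 10 | 3.14 | 1.0 | 6.2% |
| 10% | 20 | 3.14 | 2.0 | 9.8% |
| 20% | 10 | 3.21 | 2.0 | 9.6% |
| 20% | 20 | 3.21 | 4.0 | 23.9% |

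Outside this range the problem can be negligible: t = 5% with D = 5 gives 0.25 points and 5.1%.

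**4. Power.** Keep 30% other missingness in every arm and add the transfer loss in the community arms.

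| t | Missing, community | Missing, hospital | Power, primary contrast | Power, one community arm v hospital |
|---|---|---|---|---|
| 0 | 30% | 30% | 90.1% | 80.3% |
| 10% | 1 − 0.7 × 0.9 = 37% | 30% | 89.0% | 78.1% |
| 20% | 1 − 0.7 × 0.8 = 44% | 30% | 87.7% | 75.5% |

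The harm is bias, not loss of power.

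**5. Does the planned analysis cure it?** The main regression uses patients with 12-week data. The best- and worst-case, imputation and mixed-model analyses are there to assess the impact of missing data. They cannot restore observations that the rule itself stops, and a patient who transfers early may also lack the 4- and 8-week scores that the mixed model would use.

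**The case against.** The strongest reply is that exclusion is inferred, not stated. No section says that questionnaires stop after a transfer or that transferred patients leave the analysis. The only statement on the analysis population is the intention-to-treat sentence. The SAE list and the description of transfer in *Study interventions* do not mention withdrawal, so the sponsor may have meant withdrawal from the allocated venue only. This stands as a limit on the claim. It does not rescue the sentence, which would then be wrong as written.

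A reader might go further and infer that the trial will compare community successes with all hospital patients, so that its result must be biased towards community care. The document does not support that. The direction is likely from the grounds for transfer but not certain: a patient may ask to move for reasons unrelated to emotional function at 12 weeks.

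The size also depends wholly on assumed inputs. The upper case uses a gap twice the target difference and an unadjusted comparison. The planned adjustment for baseline score and for stratifiers such as performance status and treatment intent could shrink the gap.

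The *Statistical Analysis* section does address differential missingness, and that counts in the plan's favour. Its methods would help to show the loss but would not replace the data.

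Nor should one infer that GP records are lost. The request is timed thus: "Once a patient has completed the trial, a letter is sent". Since *Study interventions* allows completion to come early through withdrawal, the letter can still go out.

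**Conclusion.** The contradiction is real and explicit: a change of venue is called withdrawal from the trial in a document that commits itself to intention-to-treat. Following the rule literally risks informative loss of 12-week data in the two community arms only, and so in the primary contrast. That is a risk created by the wording, not a demonstrated exclusion.

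Under the assumptions shown (10–20% of community patients transferred and all lost, a gap of 10–20 points, no covariate adjustment), the bias is 1–4 points, or 10–40% of the 10-point target, with a two-sided type I error of about 6–24%. The true transfer share and score gap are unknown, so these figures give a scale and are not estimates. The stated sample size and power stand if transferred patients remain in follow-up. The point should be settled before or during follow-up, because a 12-week questionnaire that was not given cannot be recovered later.

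**What to change.** Reconcile *Study duration*, *Study interventions* and *Recording and collection of data* on four points:

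1. Transfer from community to hospital is a change of treatment venue and not withdrawal from the trial.
2. Transferred patients continue all data collection on the existing Table 1 schedule: questionnaires and diary at 4, 8 and 12 weeks, CSRI at 12 weeks. The single GP-record request also applies to them.
3. They are analysed in the arm to which they were randomised.
4. *Withdrawal* means withdrawal of consent to data collection.

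The clinical rules on when a patient is transferred or reviewed in clinic stay as they are; only the end of data collection is separated from the change of venue. Nothing needs deleting from *Study interventions*, where the early review covers any early withdrawal and is not specific to transfer.

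The cost is a wording change and an instruction to sites. The 12-week data visit is already held at hospital for all arms, hospital teams already complete the 4- and 8-week forms for patients treated there, and no additional patients are needed.

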### Study procedures

The study procedures are summarised in Table 1.

**Table 1 T1:** Study measures and timing

	Data point 1: Baseline, prior to commencing treatment	Data point 2: 4** weeks into treatment	Data point 3: 8** weeks into treatment	Data point 4: 12 weeks into treatment	Data point 5: 24*** weeks into treatment
Clinic Review*	x			x	X

PS	x	x	x	x	X

Weight	x	x	x	x	

Blood tests*	x				

Radiology*	x				

EORTC QLQC30.	x	x	x	x	X

HAD, EQ-5D and Patient Satisfaction Questionnaire	x	x	x	x	X

CSRI Completion	x			x	

Patient Diary for AE Recording	x	x	x	x	X

Semi-Structured Interview	x(1 in 10 patients)			x	

*Clinic review, blood tests and radiological investigations will be carried out according to standard clinical practice at baseline and during the study period.

** +/- 1 Week

*** For patients whose treatment continues beyond 12 weeks, patients will complete a further set of trial assessments when their treatment stops or at 24 weeks, whichever is sooner. This data point is optional.

### Outcome measures

#### Study end points

##### 1) Primary end point: Patient perceived benefit

Patient perceived benefit is quantitatively measured by determining overall quality of life using the EORTC QLQC30 instrument. The mean quality of life emotional function score will be compared between study populations, since this domain might be considered to best reflect the levels of anxiety and satisfaction felt by patients taking part in this study.

The QLQC30 questionnaire will be administered prior to randomisation, at 4 weeks, 8 weeks and 12 weeks. Where patients continued to receive the same treatment beyond 12 weeks, they are asked to complete a similar questionnaire once more when their treatment stopped, or at 24 weeks, whichever is sooner. Where a carer is identified, the carer is also asked to complete EORTC QLQC30 questionnaire at each time point.

##### 2) Secondary end points

###### i) *Additional patient perceived benefits*

Additional comparisons of global quality of life, anxiety and overall satisfaction with treatment received are made by asking patients to complete three additional questionnaires, as follows:

- The EQ-5D (EuroQol) instrument

- The Hospital Anxiety and Depression (HAD) questionnaire

- A specifically designed patient satisfaction questionnaire

Each questionnaire is completed prior to randomisation, at 4 weeks, 8 weeks and 12 weeks. Where patients continue to receive the same treatment beyond 12 weeks, they are asked to complete a similar set of questionnaires when their treatment stopped or at 24 weeks, whichever is sooner. Where a carer is identified, the carer was also asked to complete the three questionnaires at each time point.

###### ii) *Semi-quantitative interviews*

To triangulate the quantitative patient data, prior to commencing treatment and after 12 weeks, one in every 10 patients (and main carer if available) is randomly selected in each arm, during the main randomisation, and asked to undertake a semi-structured interview to ask specifically about their experiences relating to the treatment received. Since the perceptions and experience of staff responsible for the service is also considered to be important, 12 clinicians responsible for patients entering the trial (at least 2 from WSH, the remainder from CUH), 1 doctors from each GP Surgery, 6 treatment delivery nurses (2 from WSH, 4 from CUH) and 2 senior level Oncology Managers at each hospital are being interviewed prior to and on completion of the study. All interviews are recorded, transcribed and subsequently analysed using a Framework approach.

###### iii) *Service use and cost data*

Service use and cost data relating to patients, the NHS and society as a whole, is collected and compared for all arms of the study. Use of the specific cancer drug treatments is centrally recorded. Other service use data was collected using an adapted version of the CSRI [15]. The CSRI has been used in around 200 health economic studies of health and social care interventions in the UK and internationally. Service use information is typically provided by the patient and/or family members (supplemented where possible with administrative data from providers) and the objective is to allow comprehensive costs to be generated.

By means of the adapted CSRI, patients are asked to provide information on a range of services used, taking place at Baseline and at 12 weeks. Services include contacts with staff directly related to the delivery of cancer care (oncologists, nursing staff, hospital-based pharmacists, etc), plus other healthcare professionals (GPs, primary care nurses, psychologists, etc), and social care professionals. Time spent in hospital (overnight stays plus day-patient attendances) is recorded. In addition, time per week spent by family/friends providing care (broken down into specific tasks) to the patient because of their condition is recorded.

A key cost is thought to be related to time spent travelling by patients and/or staff, to receive or deliver treatment. Patients are asked to state where contacts take place and time spent travelling to use them and also mode of travel. Many patients are accompanied and the CSRI also records information on this. A further section in the CSRI records time taken off work by patients and family members specifically because of the condition and treatment.

Data is also collected from the chemotherapy nurses. They are asked to document all scheduled and unscheduled contact with their patients as well as working hours relating to treatment of trial patients.

Unit costs are attached to the service use data to produce service costs for each patient in the study. The costs of delivering treatment in hospital, GP surgeries and at home are derived from information on salary costs, administrative and capital overheads, and drug costs. The unit costs of other services are obtained from nationally applicable data [16]. The cost of a home care worker is used to value care provided by family members/friends. Travel time costs are estimated using wage rates for those in employment and a proportion of this for those who are not in work.

Costs are compared between the three groups using bootstrap methods to account for the likely non-normal distribution of the data. Cost-effectiveness is assessed by combining service cost data with the primary outcome measure (QLQ-C30) and also Quality Adjusted Life Year (QALYs) generated from the EQ-5D [17]. Two-way comparisons are made between the groups. If one group has lower costs and better outcome over another then it would be dominant. If costs are higher and outcome better then incremental cost-effectiveness ratios would be constructed which will show the extra cost incurred to achieve an extra unit of outcome. To address uncertainty in the cost and outcome differences, cost-effectiveness acceptability curves are used which will show the probability that one option is more cost-effective than another for different values placed on a unit improvement in outcome.

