### Eligibility

Cancer patients over 18 years of age being treated at either CUH or WSH with standard infusions of under 4 hours duration and living within a 30 minute drive of either hospital will be offered entry to this study. Eligible patients must give written informed consent and be about to commence a course of treatment planned to last a minimum of 12 weeks, or have already commenced a course of treatment which is planned to continue for a minimum of 12 further weeks. The course of treatment may be aimed at cure, palliation (disease control and life prolongation) or supportive care (symptom control). Patients need to have hot and cold running water in the home, an indoor toilet and a working telephone. Patients must be ECOG performance status < 2, or if ECOG PS 2, there must be a second individual living in the home who functions as a carer.

Patients with life expectancy under 6 months or those dependent on hospital transport are excluded. Other exclusion criteria are: any patient receiving an unlicensed cancer drug treatment as part of a clinical trial where the drug is defined as an Investigational Medicinal Product unless the trial itself has received ethics and R&D approval to be conducted in designated community settings used in the Outreach trial: patients with language barriers or communication difficulties whose safety might potentially be comprised by entry into this trial: any patient where in the opinion of the Investigator entry into this trial would give cause for concern regarding patient or staff safety.

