### Concomitant medication

Patients may receive all concomitant therapy deemed to provide adequate supportive care. Since this trial is not directly interested in treatment *per se*, concomitant medications will not be systematically recorded. However, information about ongoing treatment at the time of study entry and changes in treatment during the course of the study will be recorded by the patient in the Client Service Receipt Inventory (CSRI). In addition, records of drugs prescribed by the hospital and the patient's own GP will be obtained.

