#### Serious adverse events

For the purposes of this trial, a serious adverse event (SAE) was defined as including any event which:

- results in death, regardless of cause.

- is life-threatening (immediate risk of death).

- requires hospitalisation or prolongation of existing hospitalisation, excluding those planned for cancer treatment, disease related procedures, or placement of an indwelling catheter, unless associated with other serious events.

- results in persistent or significant disability/incapacity.

- consists of a congenital abnormality of birth defect.

- involves grade 3 or 4 (severe or life threatening) drug-related toxicities.

- results in the patient's treatment being switched from the community to hospital-based treatment.

This trial is not evaluating treatment *per se*, but the venue of treatment delivery. Thus, reporting of drug-related AEs is limited to reporting of severe or life threatening toxicities, according to National Cancer Institute, Common Toxicity Criteria.

All SAEs which occur from randomisation until the final trial visit are recorded. All SAEs are reported to the CCTC immediately, by completing an SAE form, and assessed by the Chief Investigator. Autopsy data, where available, for deaths occurring from randomisation until 28 days after the last planned treatment administration are provided to the CCTC.

The relationship of SAEs to treatment delivery venue is assessed using the following definitions:

- Not related - The adverse event would definitely have occurred whatever the venue

- Unlikely to be related - The adverse event would probably have occurred whatever the venue

- Possibly related - The adverse event had a timely relationship to treatment venue. However, a potential alternative aetiology existed.

- Probably related - The adverse event had a timely relationship to treatment venue and a potential alternative aetiology was not apparent.

- Definitely related - The adverse event had a timely relationship to treatment venue and a potential alternative aetiology was not apparent. Upon switching treatment to hospital-based delivery, the adverse event would definitely not occur.

'Unlikely' and 'Not related' are considered not treatment venue related. 'Definitely', 'Probably' and 'Possibly' are considered treatment venue related.

In the case of an SAE, the subject will be followed up until recovery or stabilisation. The Investigator will take all measures necessary to resolve any SAE.

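### Drug price sits inside the per-patient venue cost with no stated adjustment for regimen, which costs precision and allows chance imbalance in the cost comparison

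*Protocol article*

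**What the plan says.** Under Service use and cost data, drug consumption is captured by drug: "Use of the specific cancer drug treatments is centrally recorded". Patient-level totals follow: "Unit costs are attached to the service use data to produce service costs for each patient in the study". The delivery costs for hospital, surgery and home are "derived from information on salary costs, administrative and capital overheads, and drug costs". The comparison is described in one sentence: "Costs are compared between the three groups using bootstrap methods to account for the likely non-normal distribution of the data". The same service cost is then combined with the QLQ-C30 and with EQ-5D QALYs to give incremental ratios and acceptability curves.

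Elsewhere the article separates venue from drug. Under Serious adverse events it says that the object of study is not treatment as such, "but the venue of treatment delivery". Under Concomitant medication it gives as a reason for limited recording: "Since this trial is not directly interested in treatment" for its own sake.

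Eligibility admits standard infusions shorter than 4 hours with curative, palliative or supportive intent, and names no disease site. The Treatment plan section leaves prescribing to local practice in all arms. Minimisation uses centre, intent, performance status, gender and prior cancer drug treatment. Regimen, drug and number of administrations are not among the factors.

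**The concern.** The economic question is what changing the venue does to cost. A patient's regimen price depends mainly on the disease and on what the clinician would prescribe anywhere. Once it is included in the outcome, it adds between-patient variance that venue did not cause. In a trial of this size, one arm may also by chance hold more patients on expensive regimens. The cost difference, the incremental ratios and the acceptability curves would then partly reflect that chance mix.

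Cost and cost-effectiveness are the third secondary aim, and the article says the trial is meant to inform commissioning. The sample size was set on emotional function only, so nothing in the design secures precision for cost.

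**Working it through.** **The plan's own figure.** From Sample size: difference 10, SD 24, 5% level (taken as two-sided), 80% power, 30% loss.

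- Evaluable per arm: 2 × (1.96 + 0.8416)² × 24² / 10² = 90.4, so 91.
- Randomised per arm: 91 / 0.70 = 130, as stated.
- Power is 80.3% for 91 v 91 and 90.1% for 182 v 91, which agrees with the stated 80% and 90%.

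The sample size reproduces, but it concerns the QLQ-C30 and not cost.

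**Cost precision.** The documents give no cost SD, so every SD here is an assumption, in pounds per patient over 12 weeks. Drug and non-drug cost are taken as independent. The number analysed is 182 community v 91 hospital, which assumes the 30% loss also applies to cost data.

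- Total SD = √(non-drug SD² + drug SD²)
- 95% half-width = 1.96 × total SD × √(1/182 + 1/91) = 0.2516 × total SD
- Information kept = (non-drug SD / total SD)²

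| Non-drug SD | Drug SD | Total SD | Half-width | Information kept |
|---|---|---|---|---|
| 1,500 | 0 | 1,500 | 377 | 100% |
| 1,500 | 2,000 | 2,500 | 629 | 36% |
| 1,500 | 5,000 | 5,220 | 1,314 | 8% |
| 1,500 | 8,000 | 8,139 | 2,048 | 3% |
| 2,500 | 0 | 2,500 | 629 | 100% |
| 2,500 | 2,000 | 3,202 | 806 | 61% |
| 2,500 | 5,000 | 5,590 | 1,407 | 20% |

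**Mild case.** If drug SD is at most equal to non-drug SD, the standard error is multiplied by at most √2 = 1.41, and at least half the information is kept.

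**Effect on power.** For two arms of 91, non-drug SD 1,000 and a true venue difference of 500, power is 92% with no drug variation, 67% with drug SD 1,000 and 19% with drug SD 3,000.

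**Chance imbalance.** At full recruitment, 260 v 130, the SD of the arm difference in mean drug price is drug SD × √(1/260 + 1/130) = 0.1074 × drug SD. This gives 215, 537 and 859 for drug SDs of 2,000, 5,000 and 8,000. The calculation assumes simple randomisation. Minimisation on intent and prior treatment would reduce these figures by an amount the documents do not allow one to compute.

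**The case against.** Several objections carry weight.

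- **This is imprecision, not bias.** A reader might infer that the cost comparison is biased. It is not: randomisation leaves the expected venue difference unchanged, and bootstrap intervals and acceptability curves would display the added uncertainty, though not remove it.
- **Part of the spread is already controlled.** A reader might infer that nothing limits regimen mix. In fact treatment intent and prior drug treatment are minimisation factors, and the Patient safety section requires each treatment to meet the Cancer Treatment in the Community policy, which selects low-risk treatments. Price variation within those limits remains.
- **The article is condensed.** A bootstrap can be applied to a regression, and Statistical Analysis has a general rule adjusting continuous outcomes for stratifiers and baseline. Whether that rule covers cost is unclear. If it does, it still contains no regimen or price term. Baseline cost would be a weak substitute, because patients about to start have no earlier drug cost for this course. What the article does fix is that drug cost is in the outcome, and that choice is the point at issue.
- **Total cost is a legitimate outcome.** Venue could alter drug use through waste, deferral or early stopping. This stands, and it is why drug cost should not simply be dropped.
- **The size is assumed.** A reader might infer from the larger SDs that regimen price swamps the comparison. The documents do not support that as a fact. The costing also covers hospital stays, informal care, travel and time off work, so a large non-drug SD is plausible.

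**Conclusion.** The point holds as a matter of efficiency. Drug cost is put into the venue cost, no adjustment for regimen price is stated, and existing features control regimen mix only in part. The likely result is wider intervals and possible chance imbalance in the cost difference, ratios and acceptability curves.

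The size depends on cost SDs that the documents do not give. It runs from at most a 1.4-fold rise in standard error, when drug SD does not exceed non-drug SD, to 8% of the information kept with drug SD 5,000 and non-drug SD 1,500. These figures also assume independent cost components and 30% loss of cost data. The primary end point is unaffected.

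**What to change.** 1. Record the intended regimen and intended number of administrations at registration, before allocation is known. The Treatment plan section places definition of the full plan after randomisation, so this is a small change of procedure. It is feasible because eligibility and the community treatment policy already require the type and planned length of treatment to be known at entry. A regimen recorded only after allocation would not be a safe baseline covariate.
2. Price these planned courses from one common price list.
3. Analyse total cost, including actual drug use, in a bootstrapped regression with planned drug cost and the randomisation stratifiers as covariates, and carry that adjusted cost into the ratios and acceptability curves. Planned cost is fixed before randomisation, so the expected arm difference is unchanged and any venue effect on waste or omitted doses is kept. Use a covariate rather than subtracting planned from actual cost: the two are not equivalent, since subtraction forces a slope of 1.
4. Report cost excluding drug acquisition price alongside.

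The gain is limited to the part of drug-cost variance that planned cost predicts, so the losses in the table are the most that could be recovered from drug price. The cost is one registration field, a costing column, a sentence in the analysis plan and one extra cost table.
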